**Methods/Design:**

This 2-site parallel intervention trial will recruit 60 older hemodialysis patients from two urban hospitals. The trial will compare the film + a 16-week exercise program in one hospital, with a 16-week exercise-only program in another hospital. Physical fitness and activity measures will be performed at baseline, 8 and 16 weeks, and 12 weeks after the end of the program. These include the 2-min Walk Test, Grip Strength, Duke Activity Status Index, and the Timed Up-and-Go Test, as well as wearing a pedometer for one week. Throughout the 16-week exercise program, and at 12 weeks after, we will record patients’ exercise using the Godin Leisure-time Exercise Questionnaire. Patients will also keep a diary of the exercise that they do at home on non-dialysis days. Qualitative interviews, conducted at baseline, 8, and 16 weeks, will explore the impact of *Fit for Dialysis* on the knowledge/attitudes of patients, family caregivers, and nephrology staff regarding exercise for wellness, and in what ways the film is effective in educating, motivating, or sustaining patient exercise during dialysis, at home, and in the community.

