^a^To be completed each week of the intervention, and at 12 weeks post-intervention

^b^To be completed each week of the intervention

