*The Timed-Up-and-Go (TUG)*: The TUG is a test of basic mobility and reflects the ability to transfer from sitting to standing and to walk a short distance (3 m) and return to a seated position [54]. After a practice trial, the final two trials will be recorded and the best measure will be used for analysis [54]. Reliability and validity [55, 56] are well established. The TUG will be administered at baseline, 8 and 16 weeks, and 12 week after the end of the intervention.
*Godin Leisure-Time Exercise Questionnaire (GLTEQ)*: The GLTEQ is a simple 3-item measure assessing the frequency of mild, moderate, and strenuous bouts of exercise performed for at least 15 min in duration in a typical week. It will be used to capture a range of activities undertaken by patients (e.g. housework, recreational activities), as well as to compensate for the inability of the pedometer to capture exercise and activity undertaken in reclined positions during HD treatment, and possible non-adherence with wearing the pedometer. Co-I SA has successfully used this measure in exercise trials with adult cancer patients [57, 58]. It has also been validated in studies with older adults with other chronic illnesses [59–61]. On a weekly basis throughout the 16-week intervention, and at 12 weeks after the end of the intervention, the PTAs will contact patients by phone to record how much exercise was done that week using the GLTEQ [62].
*Pedometer*: Pedometers are a widely used method for inferring activity levels based on the number of steps taken throughout the day [63, 64] and considered the gold standard in physical activity measurement [65]. Patients will be asked to wear a pedometer for 1 week at baseline, and at the 8- and 16-week assessments, and 12 weeks after the end of the intervention (to facilitate comparison with the GLTEQ measured at those time points). The PTAs will download the data from the pedometer at each assessment point. Compliance with wearing a pedometer, and its validity as a measure of exercise have both been demonstrated in older adults with various chronic illnesses [64, 66].

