To explore the impact of *Fit for Dialysis* on patient fitness and activity outcomes, while keeping in mind the phase of research, our focus is to estimate change in each of the 6 measures using a hospital X time linear repeated measures model for each outcome. The 2MWT is our primary outcome. Examining hospital-level effects will allow us to determine if the two hospitals were similar at baseline. Examining time effects within each hospital will provide information on the effects of the intervention in that hospital (film + exercise or exercise-only). Additionally, examining the hospital X time interaction will allow us to determine the additional effect of the film in addition to the exercise intervention. Since this is an early-phase intervention trial and it is unclear which of our quantitative outcomes will be most responsive in this population, we will also examine the responsiveness of each of the 6 outcome measures using standardized response mean to gauge whether the film + exercise is associated with a small, moderate, or large effect size [78] for each outcome. Covariates will be similar to Primary Objective 2. To examine the impact of adherence on the 2MWT, we will include a dichotomous variable reflecting global (intradialytic and home/community-based exercise considered together) adherence (yes/no). We will also explore including the two separate adherence components (intradialytic and home/community) in the repeated measures model, recognizing the risks of collinearity and model over-fitting (with 8 variables and 60 patients, including an interaction term between the two adherence variables).

As an exploratory analysis to get an initial sense of the temporal effects of both the film and the exercise program, we will calculate change scores for each of the 6 measures from baseline to 8 weeks, from 8 to 16 weeks, and from 16 weeks to 12 weeks after the end of the intervention (i.e. 28 weeks after baseline). An additional exploratory analysis will examine the six outcome measures (DASI, GLTEQ, TUG, 2MWT, Grip Strength, and pedometer) at 12 weeks after the end of the intervention. This analysis will consist of a linear repeated measures model similar to above, with two time points (8 and 16 weeks) and 12 weeks follow-up, and will examine whether any observed gains during the intervention period persist, continue to improve further, or become attenuated over time in both the film + exercise and exercise-only hospitals.

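### The GLTEQ has no scheduled pre-intervention administration, yet the Analysis section treats it as one of six measures with a baseline

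*Protocol article*

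**What the plan says.** The schedule of the GLTEQ is stated three times in the protocol article.

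- Abstract, Methods/Design: "Throughout the 16-week exercise program, and at 12 weeks after, we will record" exercise with the GLTEQ. The same paragraph says of the other measures: "Physical fitness and activity measures will be performed at baseline, 8 and 16 weeks, and 12 weeks after the end of the program". The list that follows names the 2MWT, grip strength, DASI, TUG and pedometer, but not the GLTEQ.
- Table 1, footnote a: "To be completed each week of the intervention, and at 12 weeks post-intervention".
- Data collection, GLTEQ paragraph: "On a weekly basis throughout the 16-week intervention, and at 12 weeks after the end of the intervention", the physiotherapy assistants phone patients to record that week's exercise.

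The pedometer paragraph in Data collection points the other way. It schedules the pedometer at baseline, 8 weeks, 16 weeks and 12 weeks after the program, and gives as the reason "to facilitate comparison with the GLTEQ measured at those time points".

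The Analysis section counts the GLTEQ among "the six outcome measures (DASI, GLTEQ, TUG, 2MWT, Grip Strength, and pedometer"). For each of the six it plans a hospital × time repeated measures model, a standardized response mean, and change scores over three intervals: "we will calculate change scores for each of the 6 measures from baseline to 8 weeks", then 8 to 16 weeks, then 16 weeks to the follow-up at week 28. Of the hospital term in the model it says: "Examining hospital-level effects will allow us to determine if the two hospitals were similar at baseline".

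**The concern.** Three planned GLTEQ results need a value taken before the film and the program: the first change score, the baseline comparison of the hospitals, and a standardized response mean measured from baseline. The stated schedule provides no such value, and no later analysis can recover one that was not collected.

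This matters for three reasons. First, the third primary objective concerns the film's impact on fitness and activity, and the GLTEQ was included to cover what the pedometer misses: activity in reclined positions during dialysis, and weeks when the device is not worn. Second, there is one hospital per arm, so hospital and film cannot be separated, and a pre-film value is the only direct way to see whether the hospitals already differed on this measure. Third, the responsiveness analysis is there because it is unclear which outcome will respond most, and the study is meant to inform a Phase III trial. A GLTEQ figure that starts from a different point could not be set beside the other five.

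**Working it through.** No stated figure has to be reproduced; the check sets the schedule against the analyses.

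**Step 1: assessment weeks as stated.**

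- 2MWT, DASI, TUG, grip strength, pedometer (Data collection; Table 1): weeks 0, 8, 16, 28.
- GLTEQ (Abstract; Table 1 footnote a; Data collection): weeks 1 to 16, and 16 + 12 = week 28.

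**Step 2: are both endpoints available?**

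| Measure | 0 to 8 | 8 to 16 | 16 to 28 |
|---|---|---|---|
| Each of the five others | yes | yes | yes |
| GLTEQ | **no** (week 0 missing) | yes | yes |

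Planned change scores: 6 × 3 = 18. Computable: 5 × 3 + 2 = 17. The missing one covers the interval in which both the film and the program begin.

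**Step 3: could Table 1 supply the baseline?** The GLTEQ row has no T0 dot. It has dashes that begin in the T0 column. The intradialytic and home/community log rows have the same dashes there, and footnote b confines those logs to the weeks of the intervention. The dashes therefore mark a continuous span, and footnote a says which span applies to the GLTEQ.

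**Step 4: the other baseline-dependent results.**

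- Baseline comparison of hospitals: needs GLTEQ values at week 0 from both sites; none are scheduled.
- Standardized response mean = mean change ÷ SD of change. The Analysis section does not state the interval. If it runs from baseline, as I assume, it has no starting value for the GLTEQ.
- Hospital × time model: can be fitted to weeks 1 to 16 and week 28, but describes only how the hospitals diverge after the program has started.
- The additional exploratory model at 8 weeks, 16 weeks and follow-up: needs no week-0 value.

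**Step 5: what if week 1 stood in for baseline?** The protocol does not propose this, but it is the nearest scheduled value. For one hospital, let B be the mean before the program, W the week-1 mean and E the week-8 mean.

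- Change from baseline: E − B.
- Change from week 1: E − W.
- Amount absorbed: (E − B) − (E − W) = W − B.

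For the difference between hospitals, the amount absorbed is (W − B) at the film hospital minus (W − B) at the exercise-only hospital. An early program effect of equal size at both sites cancels from this contrast; an early effect of the film does not. The documents give no figures for B or W, so neither amount can be put in numbers.

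**The case against.** The strongest objection is that the document is divided, so a baseline GLTEQ may have been intended. The pedometer paragraph speaks of the GLTEQ at time points that include baseline, and the Analysis section writes as if the value exists. That stands as evidence of intent, and the schedule wording may simply omit a T0 administration. It does not schedule one, though, and it conflicts with three explicit statements. On either reading the text needs correcting.

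A second objection is that little depends on it. Much of this also stands. The 2MWT is the primary outcome and is untouched. The change-score analysis is labelled exploratory. Intradialytic exercise is logged separately by the physiotherapy assistants, and the DASI and pedometer are both taken at T0, so baseline activity can be compared on other measures. The GLTEQ-based home/community adherence measure needs no baseline.

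Three stronger readings are tempting, and the documents do not support them.

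- *That no GLTEQ effect can be estimated.* Two of its three change scores and a model on in-program weeks remain available.
- *That patients start from zero, so the lost change equals the prescribed exercise.* The eligibility criterion excludes only structured exercise at least 3 times a week for at least 10 minutes per session, and the GLTEQ also captures housework and recreation. Baseline values are unknown. Both hospitals receive the program, so such a change within each hospital would not be a film effect in any case.
- *That the film effect is biased toward zero.* This would need week 1 to be used as baseline, which the protocol does not propose, and a film effect already present in that week, which nothing shows.

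**Conclusion.** The point holds as an inconsistency between schedule and analysis for one non-primary measure. If the stated schedule is followed, the GLTEQ change from baseline to 8 weeks, the GLTEQ comparison of the hospitals at baseline and a baseline-referenced standardized response mean cannot be computed. That is 1 of 18 change scores plus the two related summaries.

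The conclusion rests on taking the three explicit schedule statements over the pedometer remark, and on reading the Table 1 dashes as they must be read for the exercise logs. That week 1 follows the film is a reasonable inference, since viewing comes after baseline data collection, but the article does not date the film against program week 1. Week 1 is inside the exercise program in any event.

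It should be corrected: the remedy is small and has to be applied before patients start.

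**What to change.** Add one GLTEQ administration at T0, in the baseline pedometer week and before film viewing and exercise, at both hospitals. State it in the Abstract, in Table 1 (a T0 dot in the GLTEQ row), in footnote a and in the GLTEQ paragraph of Data collection, so that these agree with the pedometer paragraph and the Analysis section. Use that value as the baseline in the GLTEQ analyses. If a T0 administration was always intended, only the wording needs correcting.

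If patients are already enrolled without it, drop the GLTEQ only from the baseline-referenced analyses: the baseline-to-8-week change, the baseline comparison of hospitals and the baseline-referenced standardized response mean. Keep the 8-to-16 and 16-to-28-week changes and the in-program model, and do not label week 1 as baseline.

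The cost is one 3-item questionnaire per patient at an existing assessment, 60 administrations at the target sample size, plus the text edits.

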## Methods/Design

### The intervention

One hospital will receive the intervention comprised of the *Fit for Dialysis* film and a 16-week exercise program involving activities during dialysis, at home, and in the community (hereafter referred to as the film + exercise hospital). The other hospital will receive the 16-week exercise-only program (hereafter referred to as the exercise-only hospital). For both hospitals there will be a 12-week post-intervention follow-up (i.e. 28 weeks after baseline).

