### Individualized exercise program

The 16-week exercise program is based on a pilot exercise program [19] developed by research team members for the >65 years HD population. It focuses on muscular strength and flexibility, cardiovascular fitness, and functional capacity. The program consists of 20–30 min of cardiovascular exercise 2–3 times per week (40–90 min per week) and 10–15 min of strengthening 2–3 times per week (20–45 min per week) with an intensity of self-reported Rating of Perceived Exertion (RPE) of ‘light’ to ‘somewhat hard’ [36] and the ability to talk without difficulty while exercising. It is based on: (a) an individualized exercise prescription appropriate to each patient’s unique functional status and current activity level (identified by standard PT assessment [37] adjusting for individual participants’ comorbidities; (b) an exercise component, using Thera-Bands™ (rubber resistance tubing) and leg cycle ergometers, to be performed during dialysis sessions and supervised and logged by a PTA; c) an exercise component, using Thera-Bands, and to the greatest extent possible patients’ daily activities and available community resources, to be performed and logged by the patient at home/in the community; and (d) plain language information sheets that identify for patients and family caregivers clear parameters for patient exercise safety.

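### The GLTEQ at weeks 8 and 16 includes the program's supervised dialysis exercise, so a week-28 fall cannot be split into the end of supervised sessions and the loss of self-directed exercise

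*Protocol article*

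**What the plan says.** **What the GLTEQ covers.** The Data collection section describes a three-item questionnaire "assessing the frequency of mild, moderate, and strenuous bouts of exercise performed for at least 15 min in duration in a typical week". One stated reason for using it is "to compensate for the inability of the pedometer to capture exercise and activity undertaken in reclined positions during HD treatment". Dialysis exercise is therefore inside the measure on purpose. The items are split by intensity, not by setting.

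**When it is taken.** The assistants telephone patients "On a weekly basis throughout the 16-week intervention, and at 12 weeks after the end of the intervention".

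**What the program delivers.** The section on the intervention describes "a 16-week exercise program involving activities during dialysis, at home, and in the community". Under Individualized exercise program, the dialysis component uses resistance bands and leg cycle ergometers and is "to be performed during dialysis sessions and supervised and logged by a PTA". Week 28 is a post-intervention visit. Study setting states that neither unit runs an exercise program of its own, and no continuation after week 16 is described. The exercise logs, for dialysis and for home/community, are kept during the intervention weeks only (Data collection and the second footnote to Table 1).

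**How it is analysed.** The last paragraph of the Analysis section plans change scores, including week 16 to week 28, and a repeated measures model at weeks 8, 16 and 28 that "will examine whether any observed gains during the intervention period persist, continue to improve further, or become attenuated over time" in both hospitals. The GLTEQ goes into both analyses alongside the other five measures, with no separation by setting.

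**A second use.** Earlier in the same Analysis section, the GLTEQ supplies the weekly minutes for home/community adherence, as though it held only that component.

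**The concern.** The other five outcomes measure walking, mobility, grip strength, self-rated function or steps. On the scope given in Data collection, the GLTEQ differs: during weeks 1 to 16 part of what it counts is the supervised intervention itself. At week 28 that supervised part is over.

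A patient who keeps up every home and community bout can therefore show a lower week-28 score only because the dialysis sessions ended. Another patient with the same fall may have given up exercising at home. The planned model would describe both as attenuation. The Background names poor follow-up adherence as a motivating problem, and the first primary objective asks about exercise sustained in three settings: during dialysis, at home and in the community. An unsplit total cannot say in which of these the gain was lost, and the results are meant to inform a Phase III trial.

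**Working it through.** The protocol gives no figure for the share of GLTEQ bouts done on dialysis, so there is nothing to reproduce. The following is a range on stated assumptions. No scoring weights are given either, so the unit is bouts per week.

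**Inputs from the protocol**
- GLTEQ threshold: bouts of at least 15 min (Data collection).
- Cardiovascular exercise: 20–30 min, 2–3 times a week. These bouts are long enough to count (Individualized exercise program).
- Strengthening: 10–15 min, 2–3 times a week. If done as separate bouts, these mostly miss the threshold (same section).
- Split of the dose between dialysis and home: not given.
- Illustrative intradialytic prescription: 60 min in a week (Analysis). In cardiovascular bouts alone this is 60/30 = 2 to 60/20 = 3 bouts.

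**Assumptions**
- I = dialysis bouts a week up to week 16, taken as 1 to 3.
- H = all other bouts a week, taken as 1 to 6, because the GLTEQ also takes in housework and recreation. H is held unchanged to week 28.
- k = share of dialysis bouts that the patient keeps up or replaces after week 16.

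**Formula**

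Week 16 = I + H. Week 28 = H + kI. Proportional fall = I(1 − k)/(I + H).

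**Result with k = 0**

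| I | H | Week 16 | Week 28 | Fall |
|---|---|---|---|---|
| 1 | 6 | 7 | 6 | 1/7 = 14% |
| 1 | 3 | 4 | 3 | 1/4 = 25% |
| 2 | 3 | 5 | 3 | 2/5 = 40% |
| 3 | 3 | 6 | 3 | 3/6 = 50% |
| 3 | 1 | 4 | 1 | 3/4 = 75% |

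**Effect of continuing (I = 3, H = 3)**
- k = 0.5: 3 × 0.5/6 = 25%.
- k = 1: 0%.

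**Between-hospital contrast**

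With k = 0 and H unchanged, the hospital × time difference is −I × (a_film − a_control), where a is the share of dialysis bouts actually done during the program.
- 70% in both hospitals, I = 3: both fall by 2.1 bouts and the difference is 0.
- 90% against 70%, I = 3: falls of 2.7 and 2.1 bouts. The film hospital loses 0.6 bouts a week more and would appear to persist less well because it did better during the program.

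**Can other data repair it?** During weeks 1 to 16 the two logs separate dialysis from home/community exercise. At week 28 no log is kept and the GLTEQ does not record setting. The pedometer is worn at weeks 8, 16 and 28 and, by the protocol's own account, does not register reclined dialysis exercise, so it gives a partial check. It counts steps, however, and would miss resistance-band work at home. No source described for week 28 supplies the split.

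**The case against.** The strongest reply is that the plan measures one quantity, weekly bouts of at least 15 min, in the same way each time. If a patient goes from five bouts to two, activity has fallen and attenuation is the right word. The Analysis section asks whether gains persist, without restricting that to self-directed exercise, and detecting loss once supervision ends is what a follow-up visit is for. This stands: the fall in the total is genuine, and the total should stay in the analysis.

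A reader might infer that the week-28 score must fall by construction. The documents do not support that. They say that the program and its logs end, not that dialysis exercise stops or that equipment is removed. Sustaining exercise during dialysis is part of a primary objective, and the adherence models include a time point 12 weeks post-intervention. If the bouts are kept up or replaced, the fall is zero.

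A reader might also infer that persistence should be judged on non-dialysis bouts alone. That goes too far, since it would hide loss in one of the three settings that the trial names. Nor is the trial wholly blind to self-directed activity, given the pedometer.

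Finally, on the reading implied by the adherence analysis, where the GLTEQ stands for home/community exercise, the problem would not arise. That reading conflicts with the purpose stated under Data collection, so it shows an inconsistency to be settled and does not answer the point.

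**Conclusion.** The point holds in a limited form. With the scope stated under Data collection, the week-28 GLTEQ is expected, not certain, to fall if dialysis bouts stop with the program, even when all other exercise is maintained. The size is about 14% to 75% on assumed counts of 1–3 dialysis and 1–6 other bouts a week with none continued, and 0% with full continuation or replacement. These counts are assumptions; the protocol gives none.

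What is lost is attribution: the persistence analysis cannot tell the end of supervised sessions from a decline in self-directed exercise. The reach is narrow. It concerns one of six measures, in analyses labelled exploratory, and leaves the primary 2-minute walk outcome untouched. The within-hospital time effect is the part mainly exposed; the hospital × time contrast is affected only if intradialytic exercise differs between hospitals. The change is still worth making before data are collected, because the split cannot be recovered for week 28 afterwards.

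**What to change.** 1. At every GLTEQ call, including the one at week 28, ask how many of the bouts at each intensity took place during dialysis.
2. In the Analysis section, report the week 8/16/28 model and the week-16-to-28 change for total GLTEQ and, separately, for bouts during and outside dialysis. State that values up to week 16 include the supervised program.
3. Reconcile the GLTEQ's scope: Data collection includes dialysis exercise, while the adherence analysis treats the questionnaire as the home/community measure. The recorded split makes either use possible.

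The cost is one more question in a call that is already planned and a few sentences of text. The small drawback is a sub-score that departs from the standard GLTEQ total; the total is still reported.
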